### Retention plan

Retention of the research participants will be one of the most important tasks of this study. Retention begins at the time of recruitment, when our research team establishes a positive rapport with the research subjects. This includes providing information in a friendly manner, being responsive to their concerns, providing women with enough detail to understand the requirements of participation and stressing the importance of the potential research findings. Special efforts that will be taken to minimize the loss to follow-up include: 1) provide reminder text messages (will be made 3 days before each study visit), 2) limit participant burden by having recruitment and survey activities conducted when women are already at the OB Center, 3) provide child care for women attending the longer group care sessions, and 4) provide incentives/compensations. In our previous prospective studies, we have achieved an excellent retention rate: 92% at delivery and 80% at postpartum visits. We were able to accomplish this through extensive follow-up with patients via phone calls and text messages, friendly research staff, and incentives that increased in value as they went through the study. For this study, we are budgeting $75 per patient (in both groups) for incentives. We will offer gift cards at: completion of randomization and the Survey 1 ($25), attending 5 visits in the assigned group treatment and completion of the Survey 2 after 30 weeks gestational age ($50).

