### Compliance, cross-over, and follow-up

Aspects of prenatal care provision and participation will be assessed through medical record review and patient surveys, to measure compliance of both groups, including detailed data for each participant’s use of prenatal care services.

Women who have a miscarriage or leave the practice and deliver their baby at a different hospital system will be treated as lost to follow-up in the final analysis. However, we will make every effort to obtain data for women who deliver at other facilities by requesting medical records when we know the location of delivery, and by obtaining their birth outcomes data through the vital statistics database with the SC Department of Health and Environmental Control.

No matter the directions and the reasons of cross-over and regardless of the number of missed prenatal care visits, participants will be kept in their original assignments, as the primary analysis follows the intent-to-treatment approach. We will also do a secondary analysis measuring outcomes “as treated,” using patients who attend at least five visits of their assigned model of care.

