### Analytic plan

Primary analyses for Aims 1, 2, and 3 will be conducted using an intent-to-treat approach. Study participants will be retained in their original assignment groups after the randomization in the analysis regardless of the number of missed visits, the use of additional services (e.g., progesterone), or loss to follow-up.
*Aim 1 analysis plan*: comparison of primary and secondary outcomes for GPNC vs. IPNC. To test the hypothesis for aim 1 that women who participated in GPNC will have a lower rate of PTB and other selected birth outcomes as compared to their counterparts in IPNC, multivariate regression models (logistic regression if the outcome is a binary variable and linear regression if the outcome is a continuous variable) will be employed with the intervention assignment as the primary independent variable. We will test the null hypothesis of coefficient of main exposure variable (GPNC vs. IPNC) equals zero. Stratified analyses will be conducted (e.g. race/ethnicity, previous history of PTB) to compare the primary and other outcomes within sub-groups.
*Aim 2 analysis plan*: comparison of racial disparities of primary and secondary outcomes for GPNC vs. IPNC. To test the hypothesis for Aim 2 that the Black-White differences in PTB and other selected birth outcomes is smaller in the GPNC as compared with that in IPNC, we will apply analyses similar to Aim 1 but adding an interaction term of prenatal care (GPNC vs. IPNC) with race (White vs. Black). We will test the null hypothesis of coefficient of interaction term equals zero. For aim 2, only women identified themselves as either Black or White will be included in the primary analysis. Then, we will conduct a sensitivity analysis to see whether including women who self-identified race as “Hispanic ethnicity”, “Mixed race” and “Other race” will influence the primary analysis results. Such sensitivity analysis will be guided by the results from the sub-groups analysis in Aim 1.

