*Aim 3 analysis plan*: comparison the effects of GPNC on maternal psychosocial (i.e. activation, engagement, stress) and behavioral (i.e. smoking, healthy eating, healthy practices) changes and exploring whether improving maternal psychosocial and health behavior outcomes will explain the potential benefits of the GPNC on racial disparities in birth outcomes. To address Aim 3, we will first test whether changes in maternal health behaviors or psychosocial factors differ by intervention and race. To do this, a similar analytic plan as used in Aim 1 & 2 will be applied, however, the dependent variables will be changes of health behaviors or psychosocial factors from baseline (~20 weeks) visit to late pregnancy (30–36 weeks). If we observe any significant differences in these health behaviors or psychosocial factors by intervention or race, the next step is to explore whether and to what extent the differences in the intermediate health behavior or psychosocial factors could explain the intervention effect or racial disparities of birth outcomes. To do so, the main multivariate regression models will be examined with and without adjustment for the intermediate health behavior or psychosocial variables.

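### The only payment for Survey 2 also requires five visits in the assigned model, so Aim 3 data are likely to be missing in relation to adherence

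*Protocol article*

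**What the plan says.** The Retention plan in the protocol article sets the total: "we are budgeting $75 per patient (in both groups) for incentives". It then names two gift cards. The first is for "completion of randomization and the Survey 1 ($25", and the second is for "attending 5 visits in the assigned group treatment and completion of the Survey 2 after 30 weeks gestational age ($50". No other payment for Survey 2 is described.

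The analysis is meant to include everyone randomised. Under Compliance, cross-over, and follow-up, "regardless of the number of missed prenatal care visits, participants will be kept in their original assignments". The Analytic plan adds: "Primary analyses for Aims 1, 2, and 3 will be conducted using an intent-to-treat approach". The same compliance section defines a secondary as-treated analysis "using patients who attend at least five visits of their assigned model of care", which is the same five-visit threshold as the gift card.

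The Aim 3 outcome needs a late-pregnancy measurement: "the dependent variables will be changes of health behaviors or psychosocial factors from baseline (~20 weeks) visit to late pregnancy (30–36 weeks". Table 2 takes the late-pregnancy psychosocial measures, and physical activity, diet and multivitamin use, from Survey 2 only. Smoking, alcohol and marijuana use is also marked for the postpartum chart review.

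**The concern.** The Retention plan lists incentives among its measures against loss to follow-up and gives them part of the credit for good retention in earlier work. As written, the larger incentive is withheld from the women most at risk of being lost: those who leave their assigned model and those who attend it little. The women paid for late-pregnancy data are the women who meet the as-treated attendance threshold, but the data are to be analysed by intention to treat.

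If payment affects response, Survey 2 responders will over-represent adherent women. This affects the Aim 3 comparison, the later step that asks whether intermediate factors explain the birth outcomes, and the process measures collected in Survey 2. If the condition is also met less often in one arm, the comparison between arms can be biased. Analysis cannot fully repair this, because the surveys were never completed.

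**Working it through.** **1. The budget.** $25 + $50 = $75, which reproduces the stated figure. Nothing remains for a Survey 2 payment that does not depend on attendance.

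**2. Who is unpaid but still analysed.** The payment rule needs five assigned visits and Survey 2. The analysis rule keeps women whatever their cross-over or missed visits. Women with fewer than five assigned visits are therefore in the Aim 3 analysis population and have no payment for the survey that supplies most of its outcomes.

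**3. Does the rule fall unequally on the arms?** The wording is the same for both. The visit schedules, taking a month as four weeks, give similar timing:
- Start at 12 weeks: the fifth group session is session 5, at 26–30 weeks (Table 1). Individual visits at 12, 16, 20, 24 and 28 weeks put the fifth at 28 weeks.
- Start at 20 weeks: the fifth group session (sessions 3 to 7) falls at 30–34 weeks. Individual visits at 20, 24 and 28 weeks, then two more at two- to three-week intervals, put the fifth at 32–34 weeks.

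The documented difference is in access. The Interventions section lets women in group care (GPNC) use extra individual visits as needed, while women in individual care (IPNC) will not attend group sessions. That makes a larger loss in GPNC possible, but the article gives no rates.

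**4. Illustration of size.** Every input here is an assumption except n = 1,580 per arm:
- s = share reaching five assigned visits
- response 0.85 if eligible for payment, and u if not
- adherent women score 0.5 SD better

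Formulas:
- response R = 0.85s + u(1 − s)
- adherent share of responders m = 0.85s / R
- bias of an arm's mean = 0.5(m − s)
- bias of the contrast = GPNC bias − IPNC bias

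| s, GPNC / IPNC | u | R, GPNC / IPNC | Bias of contrast (SD) |
|---|---|---|---|
| any | 0.85 | 85% / 85% | 0 |
| 0.90 / 0.90 | 0.50 | 81.5% / 81.5% | 0 |
| 0.80 / 0.95 | 0.70 | 82.0% / 84.3% | 0.010 |
| 0.70 / 0.90 | 0.70 | 80.5% / 83.5% | 0.011 |
| 0.70 / 0.90 | 0.50 | 74.5% / 81.5% | 0.030 |
| 0.60 / 0.90 | 0.50 | 71.0% / 81.5% | 0.040 |

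Worked example, last row:
- GPNC: R = 0.51 + 0.20 = 0.71, m = 0.51/0.71 = 0.718, bias = 0.5 × 0.118 = 0.059.
- IPNC: R = 0.765 + 0.05 = 0.815, m = 0.765/0.815 = 0.939, bias = 0.5 × 0.039 = 0.019.
- Difference: 0.040 SD towards GPNC, with 1,122 against 1,288 responders.

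In the second row the arms are balanced, but responders still over-represent adherent women (93.9% against 90%).

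**5. Scale.** With 1,343 responders per arm (0.85 × 1,580), the difference detectable with 90% power at two-sided 0.05 is (1.960 + 1.282) × √(2/1,343) = 0.125 SD. The largest bias above is about a third of that (0.040/0.125 = 0.32).

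**The case against.** The strongest reply is that payment may matter little here. Under Data collection, research nurses administer Survey 2 in person around a prenatal appointment. A woman who rarely attends would be missed whatever she is offered, and a woman who has crossed over but still attends the Center is approached face to face. This stands in part. It shrinks the group that payment could recover, mainly to cross-overs and partial attenders who can still be reached, and it means that no particular fall in response can be assumed.

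It can also be said that the rule and the sum are the same in both arms, that child care is provided for group sessions, and that paying for attendance supports adherence. All of this is fair. A reader might infer that five individual visits come almost automatically while five group sessions do not, so that the condition bears mainly on GPNC. The two schedules do not support that, and the article gives no attendance or cross-over rates.

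A reader might also take Survey 2 to be the only source for all of Aim 3. Table 2 shows otherwise for smoking, alcohol and marijuana use.

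What survives is that the rule is explicit and uses the as-treated threshold, and that separating the two conditions would keep an attendance incentive without tying the survey payment to adherence.

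**Conclusion.** The point holds as a design weakness confined to Survey 2 data. The payment rule works against an intention-to-treat Aim 3, and missingness related to adherence is likely but not certain. Its size is unknown. The illustration gives a bias from zero to a few hundredths of an SD, resting on assumed attendance, assumed response and an assumed 0.5 SD advantage for adherent women. It is zero if payment does not change response, and the bias in the arm contrast is also zero if five-visit attainment is equal in both arms under the same response assumptions.

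A reader might conclude that the Aim 3 comparison will favour GPNC or becomes adherent GPNC women against nearly all IPNC women. The documents do not support this. The direction depends on the assumed advantage and on unequal attainment, and even in the most unfavourable row above adherent women are 72% of GPNC responders against 60% of the arm.

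Preterm birth is taken from medical records and vital statistics, so Aims 1 and 2 are not affected. The change is worth making because it is cheap and the lost surveys cannot be recovered later.

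**What to change.** Pay the Survey 2 incentive on completion of Survey 2 alone, to every randomised woman still in follow-up, whatever her attendance or cross-over. If an attendance incentive is wanted, make it a separate part of the same $50. Report Survey 2 response by arm and by attainment of five assigned visits, so that the size of any adherence-related loss can be seen.

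The ceiling stays at $75 per woman, or 3,160 × $75 = $237,000 in all. Actual spending could rise within it because more women would qualify. The change needs a short ethics amendment. The downside is a weaker payment incentive to attend the assigned model.

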### Data collection

For this study, data will be collected at the following 3 time points: 1) At the time of Baseline Visit (8–23 weeks of gestational age), women will undergo group assignment and complete the baseline data collection (Survey 1); 2) After 30 weeks gestational age, research nurses will meet participants prior to or after their prenatal care appointment to administer the second survey (Survey 2); and 3) Postpartum data collection will be conducted after women attend their postpartum visit and consist of medical chart abstraction, and will not require patient contact. The study surveys will be administered electronically. Patients’ medical information will be collected from the electronic medical record (EMR). Regular data review/reports will be generated through the EMR to monitor enrollment, group balance, and the timing of the reminder calls & patient incentives. The overall timeline for study visits and data collection is summarized in Table 2.

**Table 2 Tab2:** Data collection and outcome measurement

	Gestational age <23 week (Survey 1)	Gestational age 30+ week (Survey 2)	12-week Postpartum medical chart review
Birth outcomes and pregnancy complications			
Gestational age at delivery			X
Birth weight			X
APGAR scores			X
Admission to neonatal intensive care unit (NICU)			X
Intrauterine fetal demise			X
Neonatal death			X
Pre-eclampsia			X
Gestational hypertension			X
Gestational diabetes			X
Intrauterine growth restriction			X
Macrosomia (weight >4000 g.)			X
Hospital admission during pregnancy, reason			X
Induction and reason			X
Maternal behavioral and other measures			
Maternal smoking, alcohol and marijuana use	X	X	X
Physical activity, dietary intake, and multivitamin use		X	
Maternal psychosocial measures			
Patient activation measure (PAM)	X	X	
Prenatal planning and preparation coping		X	
Prenatal anxiety, and depressive symptoms	X	X	
Shift and Persist	X		
Discrimination in prenatal care		X	
Stress management		X	
Perceived family support	X		
Support from baby’s father & relationship with baby’s father		X	
Life stressor, financial stressor and housing instability in pregnancy		X	
Perceived stress and neighborhood safety	X		
Everyday discrimination scale	X		
Role of religious on dealing with stress	X		
Adverse childhood experience	X		
Interconception care			
Attendance at postpartum visit			X
Postpartum contraception use			X
Demographics			
Race and ethnicity	X		
Age, income, education, marital status, insurance, employment, household characteristics	X		
Reproductive history			
Pre-pregnancy weight			X
Previous preterm birth			X
Number of prior pregnancies, live births, and complications			X

### Study outcomes

*The primary study outcome* is PTB (defined as birth at less than 37 weeks gestation).

#### The other study variables are

Birth outcomes and pregnancy complications: For example, birth weight; APGAR score; admission to neonatal intensive care unit; intrauterine fetal demise; neonatal death; maternal anthropometric measures; gestational weight gain; pre-eclampsia; gestational hypertension; gestational diabetes; intrauterine growth restriction; macrosomia (birth weight > 4000 g); hospital admission during pregnancy and the reason; mode of delivery; induction and reason.Maternal psychosocial measures: For example, a) Patient Activation Measure (13 items assessing confidence, knowledge, and skills in managing health and healthcare); b) Coping Inventory (15 items reflecting a range of coping strategies to manage preparing for a baby, adapted from established coping scales with additional items developed through focus groups and pilot testing with pregnant women) [43]; c) Prenatal Distress Questionnaire (a17-item scale assesses common worries and stressors during pregnancy, including concerns about labor and delivery, paying for the baby’s expenses, and managing work, relationships, and childcare) [44]; d) Perceived Stress Scale (a generalized measure assessing how overwhelmed people feel about their life circumstances [45, 46]; e) Stress Management Practices subscale of the Health Promoting Lifestyle Profile II [47, 48]; f) Prenatal Anxiety (13 items measures the emotional state of anxiety arising from women’s concerns about their pregnancy) [49]; g) Depression (The Center for Epidemiological Studies Depression Scale) [50]; h) Shift and Persist (14 item scale measures resilience) [51]; i) Everyday Discrimination Scale [52]; j) Discrimination in Prenatal Care (derived from PRAMS, Centers for Disease Control and Prevention, 2014]; k) Adverse Childhood Experience Study questions (adapted from the Behavioral Risk Factor Surveillance System questionnaire 2014 version) [53]; l) Support from Baby’s Father [54]; m) Perceived Family Support [55]; n) Role of religiosity in dealing with stress, and o) Perceived Neighborhood Safety.Maternal behavioral and other measures: for example, maternal smoking, alcohol and marijuana use; pregnancy intention; physical activity, dietary intake and multivitamin use; housing instability, access to healthcare, food insecurity, income, breastfeeding at hospital discharge and postpartum visit.Race/Ethnicity: Identifying the race of participants will be our most important quantitative measure. Indeed, the epidemiologic literature suggests that the categories of race and ethnicity reflect distinct social and environmental influences rather than actual genetic variations between populations [56–59]. We appreciate that race is more of a social than biologic construct and differences in health outcomes are likely due to the broader social and environmental differences observed between racial groups. Therefore, we will plan on using patient self-report of race and ethnicity, based on the 2020 U.S. Census categories. These categories will be used as our primary definition in the main analyses. Additionally, we will provide a narrative space for women to self-identify racial categories which do not fit neatly into the options provided, as well as questions about cultural heritage and country of origin. Finally, we will ask women about their socially assigned race and ethnicity (how an individual’s race/ethnicity is classified by others), since this has also been associated with differences in health outcomes [56, 60]. Such additional information will be used in exploratory and sensitivity analyses.Other demographic information: For example, education, employment, marital status, income, and insurance.Reproductive history: For example, pre-pregnancy weight, previous history of preterm birth, and numbers of live birth and prior pregnancies.Interconception care: For example, attendance at postpartum visit, and postpartum contraception use.

### Prenatal care process evaluation

Aspects of prenatal care provision and participation will be assessed through patient survey 2, medical record review, and existing management information systems to measure fidelity of both models and women’s experiences with care. Detailed data for each participant’s use of prenatal care services, including timing of prenatal care entry, number of visits, GPNC or IPNC visit type, provider identifier, and continuity of provider, will be collected from medical charts and will be used to describe prenatal care use.

#### In survey 2, all patients will complete

A subset of questions from the Pregnancy Empowerment Scale: to assess women’s engagement in their health care and in making their pregnancy healthy [61];Attendance of support people: Women will report who attended prenatal care with them in a supportive role and how often.

#### GPNC provision will be monitored additionally through

Perceived Cohesion Scale: This brief, four-question scale measures patients’ sense of belonging and satisfaction with their group;Adherence to GPNC educational curriculum, group size, and continuity: GPNC facilitators and the Project Coordinator currently track curriculum topics covered across sessions, group composition, and measures of GPNC fidelity for at least one session per group. These will be copied as part of data collection for this study;Annual fidelity review results: The OB Center participates in annual fidelity reviews with the Centering Healthcare Institute and has maintained high fidelity to the GPNC model since its first assessment in 2010. Fidelity reviews include a site visit by Centering Healthcare Institute faculty, record reviews, interviews, and observation. The OB Center’s fidelity results will be monitored through the study to assure key elements of the model are in place.

*IPNC provision will be monitored additionally through* medical charts review: IPNC’s educational and counseling topics will be assessed by reviewing medical charts of a randomly selected sample after women have delivered, stratified by provider.

### Mechanism for reporting adverse event

Minimal risk to the patient is associated with this study, since patients in both arms will receive prenatal care which meets or exceeds the standards set by the American College of Obstetricians and Gynecologists. We plan to report any adverse event to the IRB and the NIH as appropriate. An adverse event report form will be generated and used for collecting adverse events during the study period. Throughout the study, the Principal Investigators (PIs) (One PI is the Director and leading physician in the study site) will monitor the participants for adverse events. Events determined by the PIs to be unanticipated problems involving risks to subjects or others will be reported the IRB as in accordance with IRB policy. Adverse events that are determined by the PI to not be unanticipated problems involving risks to subjects or others will be reported per IRB policy at the time of continuing review. In addition, NIH will be notified of by the PIs of all adverse events.

